**Methods and analysis:**

We will conduct a prospective cluster randomised cross-over trial over a 6-month period, assessing the impact of an AI-assisted fracture detection tool in EDs and MIUs across 4 healthcare Trusts in the UK. Patients aged over 2 years old undergoing a plain film radiography for a suspected fracture as part of routine clinical care will be eligible for study enrolment. The trial will deploy Radiobotics’ RBfracture, a CE-approved AI-assisted medical device software for fracture detection at each site for 6 months. Randomisation will be at a cluster-level; a site will be randomised to begin with ‘AI on’ or ‘AI off’ for a month, followed by alternating active status each month for the remaining 5 months. The primary outcome will evaluate the incidence of ‘inappropriate healthcare contacts’ among patients receiving imaging for suspected fractures. This composite metric encompasses inappropriate referrals to fracture clinics, repeated hospital attendances and subsequent follow-up communications regarding missed fractures. The rates of these measures will be compared in the ‘AI on’ versus ‘AI off’ stages. Secondary outcomes will include patient-reported outcomes, clinician surveys, a predefined health economic evaluation assessing cost-effectiveness and budget impact and the diagnostic performance of the algorithm.

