### Cluster randomisation

The randomisation sequence for each cluster’s initial AI activation status (AI-on or AI-off in month 1) will be generated by a member of the study team using online randomisation software. A restricted randomisation approach will ensure balance across the three clusters, requiring at least one cluster in each starting condition; allocations assigning all clusters to the same condition will be rejected, and the first valid sequence retained. The sequence will be generated centrally, with code, random seed, and output archived in the Trial Master File to ensure reproducibility and auditability. Allocation will be implemented by the trial statistician, and the core research team will inform all sites so that they can organise locally with their PACS/informatics teams, who will be responsible for activating or deactivating the AI software as appropriate in each changeover. Following initial assignment, each cluster will follow a fixed 6-month alternating schedule (ABABAB/BABABA; figure 3). Data analysis will be undertaken by a statistician who will be blinded as to whether the AI tool was activated or inactivated within a given month.

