**Figure 3 F3:**
[figure not shown]
Example sequences of AI-activation following randomisation of clusters. AI, artificial intelligence.

This study will be divided into three clusters:

Cluster 1:Oxford University Hospitals NHS Foundation TrustJohn Radcliffe Hospital ED (level 1 ED).Horton General Hospital ED (level 1 ED).Oxford Health NHS Foundation TrustAbingdon and Witney MIUs (level 3 EDs).Cluster 2:Royal Berkshire NHS Foundation TrustRoyal Berkshire Hospital ED (level 1 ED).Henley and Townlands MIUs (level 3 ED).Cluster 3:Buckinghamshire Healthcare NHS TrustStoke Mandeville Hospital ED (level 1 ED).Stoke Mandeville MIU (level 3 ED).

Figure 3 illustrates example sequences of AI-activation following randomisation of clusters.

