### Outcome measures

The primary outcome is a measure of the proportion of ‘unnecessary healthcare contacts’, a composite measure consisting of unnecessary NHS contact resulting from false negative diagnoses, for example, phone consultations, repeat ED attendance, and those resulting from false positive diagnoses, for example, fracture clinic attendance. This will be recorded as a binary outcome, that is, whether a patient has/has not had an unnecessary healthcare contact during the follow-up period following discharge.

Secondary outcome measures include technical performance of the algorithm, and its impact on service, clinical team, and the patient. Algorithm technical performance will include:

Measures of diagnostic performance metrics against the final diagnosis provided by the radiology report.Subgroup analysis by anatomical region, fracture type, patient demographics, and other existing pathology.Number of radiographs not processed by the algorithm that fall under its intended use.Patient-reported outcomes via the EQ5D questionnaire.

The major risk from this study includes the calling of false negatives, and false positives from the AI tool. In such cases, clinicians can report specific cases of failures to the central study team. Interim analysis will identify any increases in the false negative rate over the ‘AI-on’ period. Additionally, there is a risk of over-reliance on the tool or errors in interpretation. Clinicians will be reminded to use the AI outputs as an adjunct to their clinical judgement, rather than replacing it. There is a risk of automation bias among clinicians utilising the AI tool, however all radiographs will undergo subsequent interpretation and reporting by a radiologist, reporting radiographer or other trained reporter, with relevant safety-netting protocols in place.

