### Statistical analysis

The data analysis plan has been formulated. The study design is a multiperiod treatment crossover design where treatment (the use of an AI tool) is applied sequentially over time to each site. This design has been employed to ensure a balanced distribution of AI on and AI off periods across all sites including longitudinally throughout the progress of the study to minimise the effects of any seasonal variation in injury patterns. Because the real-time presentation of AI bounding boxes may alter baseline clinician interpretive habits, diagnostic modifications could theoretically persist into subsequent control blocks (a learning or carry-over effect). To isolate and control for this potential operational bias, the primary statistical model incorporates an explicit time-dependent carry-over effect term. Within-cluster estimators will separate the direct treatment effects of active AI support from residual behavioural learning shifts across sequential monthly periods. As treatment in one period may affect the response during that period and during a later period (a carryover effect), the comparison between periods with and without the intervention can be biased. To account for any potential bias, we will use a statistical model that allows for within-subject estimators of the carryover and direct treatment effects. A linear model will be used for continuous outcomes and generalised linear models for skewed or categorical outcomes, and survival models where the outcome is time-to-event. Each model will have terms for site, period, treatment and carry-over effects. The level of statistical significance to be used in this study will be α=0.05. Subgroup analyses will explore impact of setting, algorithm, fracture type and age group.

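### The stated model has no cluster-by-month variance component, so a patient-level GLM with model-based standard errors is anti-conservative whenever monthly rates vary within clusters

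*Protocol article*

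**What the plan says.** The Abstract (Methods and analysis) sets the unit of allocation: "Randomisation will be at a cluster-level". The Cluster randomisation section says "This study will be divided into three clusters" and "each cluster will follow a fixed 6-month alternating schedule". The EDs and MIUs within a cluster therefore switch together.

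Under Outcome measures the primary outcome is binary, recorded as "whether a patient has/has not had an unnecessary healthcare contact during the follow-up period following discharge".

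The Statistical analysis section fixes the model family: "A linear model will be used for continuous outcomes and generalised linear models for skewed or categorical outcomes". It lists the terms: "Each model will have terms for site, period, treatment and carry-over effects". It sets the level: "The level of statistical significance to be used in this study will be α=0.05". It also speaks of within-cluster and within-subject estimators as the means of separating the direct treatment effect from carry-over. It names no random cluster-by-period effect, robust variance, overdispersion, cluster-month summary analysis or small-sample correction. The sample-size paragraph gives no intracluster correlation or design effect.

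**The concern.** In a cluster cross-over trial the treatment contrast is built from cluster-months. Site terms absorb lasting differences between sites, and period terms absorb changes shared by all clusters in a month. Neither absorbs a month that is unusual in one cluster only, for example through a change of staff, clinic capacity or a reporting backlog. A GLM with only the listed terms counts some 45,000 patients as independent given those terms and puts none of that variation into the standard error.

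Entering each hospital or MIU as its own site does not help, because the units in a cluster share one switching schedule. At stake are the p-value and confidence interval of the primary comparison, and of every secondary comparison of AI-on with AI-off months that uses the same model.

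**Working it through.** **Inputs from the article.** Three clusters and six monthly periods give 3 × 6 = 18 cluster-months. The recruitment aim is 45,000. The assumed rates are 5.5% without AI and 4.0% with AI, with mean (5.5 + 4.0)/2 = 4.75%. The test is two-sided at 5%.

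**Assumptions, not in the article.** Equal cluster-months of m = 45,000/18 = 2,500 patients. Two clusters start in one condition and one in the other. Carry-over lasts one month. The correlation ρ between patients in the same cluster-month, beyond site and period effects, runs from 0 to 0.002.

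**The plan's own level.** At ρ = 0 the stated model does what it claims. A simulation of the logistic GLM at a 5.5% null rate (4,000 runs) rejects in 4.8% of runs without carry-over and 5.3% with it.

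**Effect of cluster-month variation.**
- SD of the true monthly rate = √[ρ × 0.0475 × 0.9525]
- True SE / model-based SE = √[1 + (m − 1)ρ]
- Type I error = 2[1 − Φ(1.96 / SE ratio)]

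| ρ | SD of true rate (pp) | SE ratio | Type I error, formula |
|---|---|---|---|
| 0 | 0 | 1.00 | 5.0% |
| 0.00025 | 0.34 | 1.27 | 12.4% |
| 0.0005 | 0.48 | 1.50 | 19.1% |
| 0.001 | 0.67 | 1.87 | 29.5% |
| 0.002 | 0.95 | 2.45 | 42.4% |

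Worked line for ρ = 0.0005: 1 + 2,499 × 0.0005 = 2.25; √2.25 = 1.50; 1.96/1.50 = 1.31; two-sided tail 19.1%.

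Simulating the 18 proportions with binomial standard errors (20,000 runs per setting, 4.75% rate) gives about 5%, 13%, 19%, 29% and 42%, with or without carry-over. The logistic GLM with carry-over gives 19.5% at 0.0005 and 28.5% at 0.001. The SD applies independently to all 18 cluster-months, not to a single month.

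**Does the remedy hold the level?** The mean model uses 1 (intercept) + 2 (clusters) + 5 (periods) + 1 (treatment) = 9 parameters, leaving 18 − 9 = 9 df (critical value 2.26). The planned carry-over term takes one more, leaving 8 df (2.31). A residual-based t-test on the 18 proportions rejects in 4.8% to 5.2% of runs at every ρ in the table.

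**Effect on power.** For 5.5% against 4.0%, with the GLM scaled for between-cell variation and referred to t:

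| ρ | Carry-over kept (8 df) | No carry-over (9 df) |
|---|---|---|
| 0 | 63% | 100% |
| 0.0005 | 34% | 98% |
| 0.001 | 25% | 93% |

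Most of the loss comes from the carry-over term. On an alternating schedule, one-month carry-over is the complement of treatment from month 2 on, so the two separate only through month 1. The variance multiplier for treatment rises from 0.25 to 1.8125, a factor of 7.25.

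**The case against.** The strongest reply is that this is a condensed article. A full analysis plan exists, and the quoted sentence lists terms for the mean. A random effect, a robust variance or a cluster-month analysis may sit in the unseen plan, and the 18-proportion analysis proposed here uses the same terms. The Abstract also uses site for the randomised unit: "Randomisation will be at a cluster-level; a site will be randomised to begin with". So the difference between site and cluster may be partly wording.

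Part of this stands. The unseen plan may already contain the remedy, and the article does not exclude one. But the article goes beyond silence: it fixes the model family and the terms for every model, alongside a patient-level binary outcome. Run as written, that model has no place for cluster-by-month variance. The references to within-cluster and within-subject estimators say how two effects are separated, not what the error structure is.

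Two stronger readings should be resisted.
- A reader might infer that the type I error is inflated as a matter of fact. It is inflated only if cluster-month variance exceeds zero, and the article gives no value.
- A reader might infer that one odd month in one cluster could pass for an AI effect. It could not. A shift of 0.5 pp in one cluster-month moves the estimate by at most 0.5 × 1/6 = 0.083 pp, which is 0.39 of the model-based SE of 0.213 pp. With one-month carry-over the maximum is 0.50 pp against an SE of 0.573 pp, or 0.87 SE. Both fall well short of 1.96.

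**Conclusion.** The point holds as a conditional statement. The model as published omits the variance component at the level where AI status is switched. Fitted to patients with model-based standard errors, it is anti-conservative for any cluster-month variance above zero. Over the assumed range the type I error runs from 5% (ρ = 0) to about 42% (ρ = 0.002). It more than doubles, to about 12%, once true monthly rates vary with an SD of 0.34 pp on a rate of 4.75%. These figures rest on equal cluster-months of 2,500 and on assumed values of ρ. The article supports the mechanism but does not fix the size.

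**What to change.** For the primary outcome and the AI-on versus AI-off secondary comparisons, do one of two things:
- add a random effect for randomised cluster by month, with a small-sample correction; or
- analyse the 18 cluster-month proportions (or the matching summaries for other outcomes) with cluster, period, treatment and the planned carry-over term, using t on 8 df (critical value 2.31). Use 9 df and 2.26 only if carry-over is not in the model.

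Name the randomised cluster, not the individual hospital or MIU, as the clustering unit. If the analysis plan already does this, align the published description with it.

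The change affects analysis wording and programming; conduct and data collection stay as they are. The cost is wider, valid confidence intervals. The stated power of about 80% should be restated under this analysis with an explicit cluster-month correlation, because it may be materially lower when carry-over is kept: 63% at ρ = 0 and 34% at ρ = 0.0005 under the assumptions above.

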The sample size was calculated to detect an absolute difference of 1.5% in the number of inappropriate NHS contacts. We anticipate an average of 3000 skeletal radiographs for possible fracture per calendar month per Trust. Of these, on average 800 per site are anticipated to show a fracture. Assuming a baseline inappropriate NHS healthcare contact rate of 5.5% (derived from historical data evaluating fracture pathway structural adjustments), a two-sided significance level of 5% is sufficient to detect an absolute reduction to 4.0% in the primary composite outcome of inappropriate healthcare contacts at ~80% power.^24^ Overall, the study will aim to recruit 45 000 patients across all sites. Patient impact will be measured by the total number of cumulative inappropriate contacts made (ie, fracture clinic referrals for false positives, Accidentes & Emergency (A&E) reattendances for false negatives), and patient-reported outcome measures (PROMs) for overall experience of care. Impact on clinician experience of care delivery will be assessed by questionnaire. AI impact on service delivery will be measured by comparing the number of correct and incorrect fracture clinic referrals, fracture related admissions, ED recalls due to missed fractures, ED reattendances and length of stay.

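### The ~80% power is tied to no sample size, does not follow from the published inputs and 45,000 patients, and is a best case under the stated carry-over model

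*Protocol article*

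**What the plan says.** All figures are in the Statistical analysis section of the protocol article. The target effect is stated first: "The sample size was calculated to detect an absolute difference of 1.5% in the number of inappropriate NHS contacts". The AI-off rate is assumed to be 5.5%, and the power statement is that a two-sided 5% level "is sufficient to detect an absolute reduction to 4.0% in the primary composite outcome of inappropriate healthcare contacts at ~80% power". The grammatical subject of that sentence is the significance level; no number of patients appears in it. A separate sentence then gives the only total: "Overall, the study will aim to recruit 45 000 patients across all sites". No intracluster or cluster-period correlation, design effect or allowance for carry-over is given with either figure.

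The Cluster randomisation section sets out three clusters, each alternating AI on and off monthly for six months, with at least one cluster starting in each condition. On the analysis, the article says "Each model will have terms for site, period, treatment and carry-over effects", and it describes the carry-over term as part of the primary model. The primary outcome is binary per patient.

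**The concern.** A significance level cannot by itself be sufficient for a given power; a sample size must be meant, and the reader is not told which. The natural reading joins ~80% to 45,000, but for 5.5% against 4.0% that total is about seven times what a simple comparison needs. The design has only 18 cluster-months, and its schedule makes this month's and last month's treatment strongly related. It is therefore unclear whether ~80% describes the planned analysis.

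What is at stake is how a null result would be read. Depending on the model and on month-to-month variation within clusters, the published text is compatible with near-certain detection of the target effect or with power below one in four. The stated figure helps with neither.

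**Working it through.** **Inputs from the article.** Rates p1 = 0.055 and p2 = 0.040; difference 0.015; two-sided α = 0.05; total 45,000; 3 clusters × 6 months = 18 cluster-months; model terms for site, period, treatment and carry-over.

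**Assumptions made here.** Equal on/off split (22,500 each); carry-over from the previous month only, and none in month 1; cluster sizes 1:1:1 or 2:1:1, constant over months; all non-zero correlations.

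**1. The article's figure with independent patients.**
- Variance sum: 0.055 × 0.945 + 0.040 × 0.960 = 0.090375.
- n per arm for 80% power = (1.960 + 0.842)² × 0.090375 / 0.015² ≈ 3,153. The pooled-variance formula gives about 3,155, or 6,310 in total.
- At 22,500 per arm: SE = √(0.090375 / 22,500) = 0.00200; z = 0.015 / 0.00200 = 7.48; power > 99.99%.
- One-sided testing (2,486 per arm), a continuity correction (3,288) or 90% power (4,224) do not bring the requirement near 22,500.

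The ~80% is not reproduced at 45,000.

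**2. What inflation would reconcile the two?** 22,500 / 3,155 = 7.13. With m = 45,000 / 18 = 2,500 patients per cluster-month and a design effect of about 1 + m × δ, where δ is the within-period minus the between-period correlation, this needs δ ≈ 6.13 / 2,500 ≈ 0.00245. No such value is stated.

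**3. The stated model with no cluster-month variation.** I used weighted least squares on the 18 cluster-months, with average patient variance 0.090375 / 2 = 0.0451875.
- Equal clusters, without carry-over: treatment variance = 0.25 × 0.0451875 / 2,500, so SE = 0.00213.
- Equal clusters, with carry-over: the factor becomes 1.8125, so SE = √(1.8125 × 0.0451875 / 2,500) = 0.00572. The variance is multiplied by 1.8125 / 0.25 = 7.25, because in a strictly alternating schedule last month's treatment is nearly the complement of this month's.
- Other cluster sizes change the SE only through the share f of patients in one sequence, in proportion to 1/√(f(1 − f)).

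| Share in one sequence | SE | Power, normal | Power, t on 8 df |
|---|---|---|---|
| 1/2 (2:1:1, large cluster alone) | 0.00540 | 79% | 68% |
| 1/3 (equal clusters) | 0.00572 | 75% | 63% |
| 1/4 (2:1:1, large cluster with a small one) | 0.00623 | 67% | 56% |

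The 8 df are 18 cluster-months minus 10 parameters. The half-and-half split is the most efficient, so 79% is the ceiling under these assumptions.

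**4. The stated model with cluster-month variation (assumed).** For equal clusters the SE is multiplied by √(1 + 2,499δ).
- δ = 0.0005: 0.00572 × √2.25 = 0.0086; power 34% (31–35% across the three patterns; t, 8 df). By normal approximation the range is 39–43%.
- δ = 0.001: 0.00572 × √3.50 = 0.0107; power about 23% (22–24%; t, 8 df).

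These values of δ correspond to a cluster's true rate varying from month to month with SD √(0.0005 × 0.0452) = 0.48 and √(0.001 × 0.0452) = 0.67 percentage points.

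**5. For contrast, the same model without carry-over (t, 9 df).** Power is 98–99% at δ = 0.0005, 90–93% at 0.001, 71–74% at 0.002 and 40% at 0.005.

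**The case against.** The strongest defence is that the article only condenses a fuller plan. It says the full protocol and analysis plan exist, and correlations and design effects are commonly left to them. Their absence here does not show that clustering was ignored, and that stands. A reader might infer that ~80% is simply not this trial's power, or that nothing links it to 45,000. The document does not support either inference. A design effect of about 7.1 would link them. So would the carry-over model in its most favourable pattern with no cluster-month variation (79%), or the model without carry-over at δ = 0.002 under a normal approximation (81–83%). These are different calculations, and the article does not say which, if any, was done.

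Two further inferences should be resisted. Power at 3,000 per arm is 78%, which invites the guess that one month's volume was used as the arm size; the article gives 3,000 only as a monthly volume per Trust. Multiplying that volume out gives 54,000 (three clusters) or 72,000 (four Trusts) over six months, but these are radiographs. One patient can have several, and exclusions and opt-outs apply, so a target of 45,000 patients is no contradiction.

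It is also fair that part of the fall from 67–79% to 31–35% comes from moving from a normal to a t reference; the like-for-like figures are given in the working. The non-zero correlations are scenarios, not properties shown for these sites.

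None of this repairs the sentence. The article chose to publish rates, level, power and total, and as printed they do not connect.

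**Conclusion.** The point holds in this form: ~80% is attached to no sample size and does not follow from the published inputs and the 45,000 target without an unstated inflation of about 7-fold. The independent-patient arithmetic needs no assumption beyond an equal on/off split.

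For the analysis the article names as primary, ~80% is at best a ceiling. It is approached only with no cluster-month variation, a normal reference and the most favourable cluster sizes and allocation, and it falls steeply with small month-to-month variation. That part rests on a one-month carry-over and constant cluster sizes, and below the zero-variation case on assumed correlations. The article does not specify the form of its carry-over term; another form would give other figures.

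**What to change.** Replace the power sentence with the power of the actual design:

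- State the sample size to which the power refers: 45,000 patients in 3 clusters × 6 months, about 2,500 per cluster-month.
- Compute it under whichever model is declared primary, including the carry-over term, with its form stated, if that term is kept.
- Use small-sample degrees of freedom, given 18 cluster-months.
- Show power over a stated range of within- and between-period correlations, for example estimated from the sites' pre-trial monthly rates.

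If ~80% already came from such a calculation, giving its inputs is enough. Recruitment has begun, so this should be settled before any unblinded analysis. The cost is a recalculation and a few sentences; no extra enrolment is needed. The downside is that the stated power may become less favourable.
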